#### Prognosis of therapy outcome

To identify the prognostic outcome variables on upper extremity functioning, a regression analysis will be performed on the group which received mental practice training. The WMFT scores at 6 and 12 months will be introduced as the dependent variable in the model, and the following hypothesized predictors as independent variables: age, sex, brain lesion site, ability to imagine motor acts (Vividness of Movement Imagery Questionnaire; VMIQ), cognitive level (Cog-log), credibility and expectancy of training (CEQ), general arm muscle strength (WMFTtask_strength _on T0) (as presented in Table 3). The model will be adjusted for possible baseline differences on the WMFT.

**Table 3 T3:** Hypothesized predictors for treatment outcome

- age
- sex
- brain lesion site
- training expectancy and credibility
- ability to imagine motor acts
- cognitive level
- general arm muscle strength

#### Process evaluation

Entries in the patients' diaries and both the process evaluation of the patient and the occupational therapist will be analyzed descriptively.

#### Economic evaluation

Incremental ratios of differences in costs to outcomes between the intervention and control groups will be calculated. Outcomes for an incremental cost-effectiveness ratio will be changes in upper limb function primarily measured by the WMFT. QALYs generated through the utility values estimated by a specific QoL measure will be used for the incremental cost-utility ratio. These ratios will be plotted on the cost-effectiveness/utility plane to determine the economic use of one intervention over another. Level of confidence regarding economic determination will be quantified through non-parametric bootstrap simulations of the incremental ratios at the 2.5 and 97.5 percentile marks. The net-benefit framework will further validate this level by describing the acceptability probability of the net (monetary/health) benefit as a function of the ceiling ratio, or society's maximum willingness to pay. A 4-state Markov with 6-month cycle to approximate the time span between medical follow-ups will be used to simulate a long-term, 4-year period. Discounting of costs and outcomes will be undertaken at 4% [52]. Uncertainty about methodology and generalizability will be handled using a multi-way sensitivity analysis in which more than one study element (e.g., baseline subject characteristics and discounting) is varied.

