### Data collection

Measurements will be taken upon entry to the study (T0 = baseline) and 6 weeks (T1 = post treatment); 6 months (T2 = short-term follow-up); 9 months (T3 additional cost questionnaire) and 12 months (T4 = long term follow up) after T0. They will be performed by a rater blinded for therapy modality, and administered wherever the patient is at the time. A blinding check will be performed after each of the four measurement sessions.

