### Outcome measures

Outcome measures and assessment moments are presented in table 2.

**Table 2 T2:** Outcome domains and assessment instruments and moments

**Domain**	**Assessment instrument**	**Abbr.**	**T0**	**T1**	**T2**	**T3**	**T4**
Medical information	- Brain lesion		X				
	- Type of stroke		X				
	- Co-morbidity		X				
Basic level of functioning	- Barthel score	BI	X		X		X
	- Frenchay Activity Index	FAI	X*	X	X		X
Cognitive functioning	- Cognitive Log	Cog-log	X				
	- Vividness of Movement Imagery Q.	VMIQ	X				
	- Credibility/Expectancy Q.	CEQ	X				
UEF level of impairment	- Brunnstrom-Fugl-Meyer test	FM	X	X	X		X
	- Strength: part of WMFT	WMFT _str_	X	X	X		X
	- Spasticity: Tardieu scale	MTS	X	X	X		X
UEF level of activity	- Wolf Motor Function Test	WMFT	X	X	X		X
	- Frenchay Arm Test	FAT	X	X	X		X
	- Accelerometry	ACC	X	X	X		X
UEF level of participation	- Impact on Participation and Autonomy questionnaire	IPA					X
	- Stroke-Specific Quality of Life	SS-Qol					X
	- EuroQol	EO-6D		X	X		X
Cost	- Cost questionnaire	CQ	X	X	X	X	X
Process evaluation	- Diary		X				

T0 = baseline

UEF = upper extremity functioning

T1 = 10 weeks after T0

T2 = 6 months after T0

T3 = 9 months after T0

T4 = 12 months after T0

* The FAI on T0 retrospectively assesses the pre-morbid activity level

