### Determination of costs

Both direct non-medical and indirect costs will be measured using a cost questionnaire administered to the participants or their proxies at the time of the T0-T4 assessments [50]. An additional cost questionnaire will be sent to the patient at 9 months. With society's perspective for the economic evaluation, all relevant rehabilitation costs will be determined using a micro-costing approach. This means that the unit size of the resource used will be multiplied by the respective unit cost across patients to estimate the aggregate cost for society [51]. Healthcare resources used in administering the intervention as well as direct medical costs would include contact with professionals (e.g., physicians, therapists and rehabilitation nurses or formal caregivers), equipment and materials (e.g., orthoses), assessment tools, and medications (particularly anti-spasmodics and muscle relaxants). Along with allocated overhead costs, these measures will determined through the institutions' administrative records.

Direct non-medical costs include patient times, transportation and out-of-pocket expenses not covered by insurance. Indirect costs would cover productivity losses and informal care by the family or significant others. In line with recommendations in the Dutch manual for costing in economic healthcare evaluations, standardized costs will be used [52]. Medications will be valued based on the Daily Defined Dosage (DDD) price list from the Dutch Pharmacotherapeutic Compass [53]. Productivity losses will be valued using the friction cost method, which bases calculations on the 'friction period,' or the time needed to replace a sick employee. Informal care (considered unpaid work) would be valued using shadow prices.

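### No utility is measured at T0, so one-year QALYs have no measured starting value and cannot be adjusted for baseline utility

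*Protocol article*

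**What the plan says.** Cost-effectiveness is the third research question under Aims. The Economic evaluation section plans a cost-effectiveness ratio based on change in upper limb function, mainly on the WMFT, and a cost-utility ratio: "QALYs generated through the utility values estimated by a specific QoL measure will be used for the incremental cost-utility ratio". Uncertainty is to be expressed by "non-parametric bootstrap simulations of the incremental ratios at the 2.5 and 97.5 percentile marks". The same section also plans the cost-effectiveness/utility plane and a net-benefit analysis with acceptability probabilities.

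The measurement schedule is in Table 2 (Outcome measures). The EuroQol row reads "EuroQol EO-6D X X X", with the marks under T1, T2 and T4 and the T0 cell empty. The other quality-of-life instrument reads "Stroke-Specific Quality of Life SS-Qol X", its single mark being at T4. The IPA is also taken at T4 only. Costs start at entry: under Determination of costs they are "measured using a cost questionnaire administered to the participants or their proxies at the time of the T0-T4 assessments".

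The timing of T1 is given in two ways. Data collection says "Measurements will be taken upon entry to the study (T0 = baseline) and 6 weeks (T1 = post treatment", while the footnote to Table 2 says "T1 = 10 weeks after T0". The horizon is "T4 = 12 months after T0".

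**The concern.** A QALY total over the trial year is the area under each patient's utility curve from randomisation to 12 months, and that curve needs a value at its start. Here costs are counted from T0, but utility is first observed at the end of treatment. The stretch from T0 to T1 is the treatment period itself, in patients two to six weeks after stroke, so it is not safe to assume that utility is flat over it.

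Two things are lost. The first segment of the curve has to be filled by an assumption. In addition, any chance difference between the arms in starting utility stays in the QALY difference, because the covariate best suited to take it out was never recorded. Elsewhere the protocol does use a baseline: the cost-effectiveness ratio uses change in WMFT, and the prognostic model adjusts for baseline WMFT. Only the utility lacks one. An analysis plan written later can choose a method, but it cannot supply a measurement that was not taken.

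**Working it through.** The protocol gives no QALY, utility or variance figure, so there is none to reproduce. The check has four steps.

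**1. Is any utility taken at T0?** Table 2 shows:

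| Instrument | T0 | T1 | T2 | T3 | T4 |
|---|---|---|---|---|---|
| EQ-6D | – | X | X | – | X |
| SS-QoL | – | – | – | – | X |
| IPA | – | – | – | – | X |
| Cost questionnaire | X | X | X | X | X |
| WMFT, FAT, Fugl-Meyer, accelerometry | X | X | X | – | X |

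Outcomes on the full clinical schedule carry four marks and the EQ-6D carries three, so at least one of those four visits lacks it; the column layout puts the gap at T0. No other section places the EQ-6D at T0. Whichever instrument supplies the utilities, there is no baseline value.

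**2. How much of the year has no starting value?**

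- T1 at 6 weeks: 6/52 = 11.5%.
- T1 at 10 weeks: 10/52 = 19.2%.

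Under the trapezoid rule the weight of the T0 utility is half of that segment:

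- T1 at 6 weeks: w0 = (6/52)/2 = 0.058.
- T1 at 10 weeks: w0 = (10/52)/2 = 0.096.

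**3. How large can a chance T0 difference be?** The utility SD is an assumption, 0.25 to 0.30. The 80 per arm is from Study population. SE = SD × √(2/80):

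- SD 0.25: 0.0395.
- SD 0.30: 0.0474.

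A difference of 0.05 is then 0.05/0.0474 = 1.05 to 0.05/0.0395 = 1.27 standard errors, which is unremarkable.

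**4. What does a 0.05 imbalance do to the QALY difference?** Let p be the share of the imbalance that persists at T1, T2 and T4 (an assumption). The shift is 0.05 × [w0 + p × (1 − w0)].

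| p | T1 at 6 weeks | T1 at 10 weeks |
|---|---|---|
| 0 | 0.05 × 0.0577 = 0.003 | 0.05 × 0.0962 = 0.005 |
| 0.3 | 0.0029 + 0.3 × 0.05 × 0.9423 = 0.017 | 0.0048 + 0.3 × 0.05 × 0.9038 = 0.018 |
| 0.7 | 0.0029 + 0.7 × 0.05 × 0.9423 = 0.036 | 0.0048 + 0.7 × 0.05 × 0.9038 = 0.036 |

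These are shifts in the full-year difference reckoned from T0. If every patient is given the same assumed starting utility, the p = 0 part does not appear in the computed difference. The persisting part does, and it is the larger.

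**Secondary check: percentile limits of the ratio.** These were simulated with 2,000 trials and 2,000 normal draws each in place of bootstrap replicates. Assumed standard errors were 0.035 for effect and 1,000 for cost, with a mean cost difference of 1,000.

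| True effect/SE | Mean share of replicates with negative effect | Coverage of nominal 95% limits |
|---|---|---|
| 0.25 | 42.3% | 0.915 |
| 1 | 24.5% | 0.982 |
| 2 | 8.0% | 0.974 |
| 4 | 0.2% | 0.948 |
| 6 | 0.0% | 0.952 |

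The limits behave well when the effect is far from zero. They drift from nominal, and lose a clear meaning, when replicates spread over quadrants.

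**The case against.** The strongest reply is that randomisation already protects the comparison. A chance difference in starting utility is sampling error and the bootstrap reflects it, so it does not bias the estimate. That is correct. What is lost is precision and the ability to adjust for what actually happened in this sample.

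A reader might go further and infer that no analysis could deal with the imbalance. The protocol does not support that. Barthel, WMFT, Fugl-Meyer and Frenchay Arm Test scores are all taken at T0 and can serve as covariates, randomisation is stratified by elbow flexor strength and hospital, and the planned sensitivity analysis mentions baseline characteristics. These are partial substitutes, since they measure function and not utility.

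It is also fair to say that the direct weight of the T0 value is small, and that the larger figures depend on a persistence share for which the protocol gives no data. Both points stand, which is why the results are given as ranges. The scope is limited too: the primary outcomes and the WMFT-based ratio have a baseline and are untouched. Which instrument yields the utilities, and by what formula, is detail that a full plan may settle and is not counted against the article.

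A reader might also infer that percentile limits on the ratio are invalid as such. The simulation does not bear that out, and the same section already plans the plane and the net-benefit acceptability analysis, which are the usual answers. Nor can the power for the WMFT difference be used to say how often the cost-utility ratio would fail, because the protocol gives no QALY effect.

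**Conclusion.** The gap is real and is fixed by the schedule: utilities begin at T1 while costs begin at T0. The cost-utility ratio therefore rests on an assumed utility path over 11.5% or 19.2% of the year, depending on which T1 timing holds, and the QALY difference cannot be adjusted for baseline utility.

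The size depends on assumptions that the protocol does not supply, namely a utility SD of 0.25 to 0.30 and the share of an imbalance that persists. Under them an ordinary chance difference of 0.05 is worth 0.003 to 0.005 QALY without persistence and about 0.017 to 0.036 QALY with 30% to 70% persistence. This is a cheaply avoidable weakness in the answer to the third research question, and it leaves the efficacy analysis intact. The point about percentile limits is secondary and conditional on replicates crossing quadrants.

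**What to change.** - Add the EQ-6D to the T0 assessment in Table 2.
- Compute QALYs as the area under the utility curve from T0 to T4, and estimate the QALY difference with T0 utility as a covariate.
- Reconcile the 6-week and 10-week statements for T1, since they set the length of the first segment.
- Keep the plane and the net-benefit acceptability analysis as planned. State that the 2.5 and 97.5 percentile limits of the ratio will not be reported or relied on when bootstrap replicates fall in more than one quadrant.

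The cost is a six-item questionnaire with a visual analogue scale, a few minutes per patient at a visit that is already held. The statement on the ratio limits costs one sentence. For any patients whose T0 visit has passed without the EQ-6D, the value cannot be recovered. For them the plan should state the starting utility it assumes, vary it in the sensitivity analysis, and adjust for T0 measures such as Barthel or WMFT as a partial substitute.

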Thirdly, in choosing the current outcome measures, three different domains of the International Classification of Functioning (impairment, activity and participation) were included. The second domain – level of activity – was chosen as the primary outcome measure level, since changes in this domain seem most clinically relevant in daily life performance. Both the ability to perform daily activities (to be measured by the Wolf Motor Function Test) and the level of activity in a daily life situation (to be assessed using accelerometry), are included. In our opinion, additional assessment of real-world impaired arm activity by way of accelerometry is important, since discrepancies between motor capacity as measured by laboratory performance tests and its actual use in daily life can exist.

To conclude, this paper described the design of a randomized controlled clinical trial to study the effectiveness of mental practice training aimed at improving upper extremity functioning in stroke patients. The results of this study will provide evidence as to the (cost) effectiveness of the training as well as indicators for effective mental practice training in stroke patients.
